### **Primary outcome measures**

The objective remission of the primary efficacy endpoint evaluation refers to the CR, PR or MR judged by the investigator according to the RECIL 2017 Response Criteria for Malignant Lymphoma. Subjects who do not meet the above criteria, including those who have not undergone any post-baseline tumor assessment, will be evaluated as non-remission.

ORR (CR+PR) refers to the proportion of subjects who have an objective remission. The population participating in the analysis is the subjects who have been confirmed by the investigator to have evaluable or measurable lesions in the efficacy analysis.

The proportion of subjects and the corresponding 95% CI will be summarized according to the remission categories (CR, PR, SD and PD) judged by the investigator. This analysis will be determined by the investigator in the efficacy analysis set of subjects who have evaluable or measurable lesions at baseline. At the same time, the remission rate and remission category evaluated by the investigator will be summarized in the proportion of subjects and the corresponding 95% CI. This analysis will be determined by the investigator in the efficacy analysis set of subjects who have evaluable or measurable lesions at baseline.

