|                           | 
 
• Evaluate the efficacy of sintilimab plus chidamide in patients with RR-ENKTL.
 
• Identify the maximum tolerated dose (MTD), dose limited toxicities (DLTs) and recommended Phase II dosage (RP2D) of chidamide in combination with sintilimab.
 
 
Secondary Objectives
 
 
• Long-term survival of sintilimab plus chidamide in patients with RR-ENKTL.
 
• The safety profile of sintilimab plus chidamide.
 
 
Exploratory Objectives
 
Explore correlations between clinical activity and tumor and/or blood biomarkers.
                                                                                                                                                                                                                                                                     |
| Endpoints          | 
Primary Endpoint
 
Overall response rate (ORR) is defined as the proportion of patients with a best overall response of complete response (CR) or partial response (PR) according to the RECIL 2017 Response Criteria for Malignant Lymphoma as determined by investigators.
 
Secondary Endpoints
 
 
• Progression-Free Survival (PFS) is defined as the time from the treatment date to the date of recurrence, disease progression or death.
 
• Duration of Response (DoR) is defined as the date of their first objective response (which is subsequently confirmed) to disease progression or among participants who experience an objective response.
 
• Overall Survival (OS) is defined as the time from treatment to the date of death.
 
• Frequency and severity of adverse events (AEs) and serious adverse events (SAEs)
 
 |

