| plus chidamide in patients with RR-ENKTL.
• Identify the maximum tolerated dose (MTD), dose limited toxicities (DLTs) and recommended Phase II dosage (RP2D) of chidamide in combination with sintilimab. | 2017 Response Criteria for Malignant Lymphoma as determined by investigators in all treated patients; ORR is defined as the proportion of patients with a best overall response of complete response (CR) or partial response (PR).                                                                                                                                                                                                                                                                                                  |
| Secondary                                                                                                                                                                                             |                                                                                                                                                                                                                                                                                                                                                                                                                                                                                                                                      |
| • Long-term survival of sintilimab plus chidamide in patients with RR-ENKTL.
• The safety profile of sintilimab plus chidamide.                                                                           | • Progression-Free Survival (PFS) is defined as the time from the treatment date to the date of recurrence, disease progression or death.
• Duration of Response (DoR) is defined as the date of their first objective response (which is subsequently confirmed) to disease progression or Among participants who experience an objective response.
• Overall Survival (OS) is defined as the time from treatment to the date of death.
• Frequency and severity of adverse events (AEs) and serious adverse events (SAEs) |

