#### **10.4 Efficacy analysis**

The researcher can decide the patient's treatment plan based on the efficacy assessment made by the research center. Please refer to Chapter 7.1 for the definition of each efficacy endpoint. The confirmed ORR and the 95% Clopper Pearson confidence interval should be calculated. In addition, other efficacy endpoints, including PFS, DCR, DoR and OS should also be evaluated.

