|                                                                                                                                                                                                                              | CR                                                                                                                                                                                                                                         | PR                                                                          | MR a                                                                    | SD                                                                                | PD                                                                                                                                                                                                                                                                                                            |
| % Change from baseline                                                                                                                                                                                                       | 
 
• Complete disappearance of all target lesions and all nodes with long axis
 
• 30% decrease in the sum of longest diameters of target lesions (PR) with normalization of FDG-PET
 
 | 30% decrease in the sum of longest diameters of target lesions but not a CR | 10% decrease in the sum of longest diameters of target lesions but not a PR (<30%) | <10% decrease or < 20% increase in the sum of longest diameters of target lesions | 
 
• >20% increase in the sum of longest diameters of target lesions
 
• For small lymph nodes measuring <15 mm post therapy, a minimum absolute increase of 5 mm and the long diameter should exceed 15 mm
 
• Appearance of a new lesion
 
 |

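### Section 10.2 counts minor response as objective remission for the primary endpoint, while ORR is CR or PR everywhere else; confirmation of response is also required in some places and not in others

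*Protocol*

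**What the plan says.** **Who is a responder.** Protocol section 10.2, under primary outcome measures, states: "The objective remission of the primary efficacy endpoint evaluation refers to the CR, PR or MR judged by the investigator". The next sentence treats subjects who do not meet those criteria, including those never assessed after baseline, as non-remission. The following paragraph states: "ORR (CR+PR) refers to the proportion of subjects who have an objective remission". The label in that sentence excludes MR, but the term it relies on includes it. The section then has results summarised "according to the remission categories (CR, PR, SD and PD) judged by the investigator", so MR has no row.

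The synopsis and section 2 both define ORR as the proportion whose best overall response is CR or PR. Section 7.1.1 lists ORR, CR rate and PR rate, with no minor-response rate. Appendix 2 makes MR a separate, provisional RECIL category: a decrease of at least 10% but below the 30% needed for PR.

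**Confirmation.** Section 10.4 states: "The confirmed ORR and the 95% Clopper Pearson confidence interval should be calculated". The ORR definition in the synopsis and section 2 asks for no confirmation. DoR, however, is defined in the synopsis, section 2 and section 7.1.2 from a first response that is later confirmed, whereas the DoR definition in section 10.2 starts at the first CR or PR with no such condition. No rule for confirming a response is given.

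**The concern.** ORR is the only endpoint tested against a decision rule. The number of responders is compared with 4 of 7 at stage one and 19 of 28 at the end, so the responder definition fixes the operating characteristics of phase II. The MR sentence reads as the operative rule, because it is followed at once by the instruction on who counts as non-remission.

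The design rates come from section 10.1, where the cited historical ORRs are sums of CR and PR. Adding MR to the numerator raises the count without moving the null rate of 0.55. It also breaks the secondary endpoints: section 10.2 assesses DoR in subjects with objective remission but starts the clock at CR or PR, so a patient whose best response is MR would be in the DoR set with no start date.

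The trial is open-label and single-arm, and response is judged by the investigator. Two available definitions would allow the choice to be made after the responses are known, and near a boundary of 20 of 28 a single MR patient could decide the result.

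**Working it through.** **Inputs from the protocol.** Section 10.1: p0 = 0.55, p1 = 0.80; stop if 4 or fewer of 7 respond; declare activity if more than 19 of 28 respond. Synopsis: one-sided type I error 5%, power at least 80% (the β = 0.8 in section 10.1 has to be read as power). Historical tables in section 10.1: anti-PD-1 antibody 12/15, with 5 CR + 7 PR = 12; chidamide 12/20, with 6 CR + 6 PR = 12. No MR is counted in either.

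**Assumption.** The share m of patients whose best response is MR is not in the protocol. It is varied here.

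**Formula.** With counted response probability p,

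P(success) = Σ over x = 5, 6, 7 of P[Bin(7, p) = x] × P[Bin(21, p) ≥ 20 − x]

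P(stop at stage one) = P[Bin(7, p) ≤ 4].

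**The plan's own design.** A full search for the optimal Simon design at these inputs (total N up to 44) returns 4/7, 19/28, as stated.
- At p = 0.55: 0.2140 × 0.0964 + 0.0872 × 0.1971 + 0.0152 × 0.3413 = 0.0206 + 0.0172 + 0.0052 = 0.043. P(stop at stage one) = 0.684.
- At p = 0.80: 0.2753 × 0.8915 + 0.3670 × 0.9569 + 0.2097 × 0.9856 = 0.2454 + 0.3512 + 0.2067 = 0.803.

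**Counting MR.** Hold true CR+PR at the null, so the counted rate is p = 0.55 + m. For m = 0.05, p = 0.60: 0.2613 × 0.2002 + 0.1306 × 0.3495 + 0.0280 × 0.5237 = 0.113 after rounding.

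| Assumed MR share | Counted rate | False-positive rate | Stop at stage one |
|---|---|---|---|
| 0 points | 0.55 | 4.3% | 68.4% |
| 2 points | 0.57 | 6.5% | 64.4% |
| 5 points | 0.60 | 11.3% | 58.0% |
| 10 points | 0.65 | 24.0% | 46.8% |

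The stated 5% is exceeded at 2 points, and the futility look weakens at the same time.

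**Requiring confirmation.** If a fraction c of CR/PR is confirmed (an assumption), the counted rate is c × p.
- c = 0.95: power at 0.95 × 0.80 = 0.76 is 0.667; type I error at 0.95 × 0.55 = 0.5225 is 0.023.
- c = 0.90: power at 0.90 × 0.80 = 0.72 is 0.506; type I error at 0.90 × 0.55 = 0.495 is 0.011.

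This effect runs opposite to that of counting MR.

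**The case against.** The strongest reply is that MR was never meant to count. The formal definitions in the synopsis and section 2 agree and are clear. Section 10.2 itself labels ORR as CR+PR and tabulates without MR. Section 7.1.1 names no minor-response rate, and both TTR and DoR are tied to CR or PR. On this view one stray term sits in the analysis section, and the DoR gap is evidence of intent more than a further defect. This stands as to the likely intent. It does not remove the contradiction, because the outlying sentence is the one that sorts subjects into remission and non-remission.

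The size can also be challenged. No MR rate is given, and because the endpoint is best response, only patients who never improve beyond MR would add to the count. That is correct: the percentages are illustrations under assumption, and only the direction is certain. Section 10.1 also says merely that the rates follow previous studies, and 0.55 equals neither table's ORR (80% and 60%). The CR+PR scale of p0 is therefore inferred from the tables and not stated.

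A reader might infer that the trial's type I error is inflated as designed, or that the confirmation wording adds to the inflation. The documents support neither. The first holds only if the MR sentence governs the count; the second has the wrong sign.

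**Conclusion.** The concern holds as a contradiction in the definition of the primary endpoint. Section 10.2 admits MR as objective remission, against its own label and tabulation and against the synopsis and section 2. Because it is the responder rule for both stages, it should be corrected even though most of the protocol points to CR+PR.

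If the MR sentence were followed, and CR+PR were truly 55%, the false-positive rate would be 6.5%, 11.3% or 24.0% for assumed MR shares of 2, 5 or 10 points, against 4.3% as designed. These figures rest on an MR share that the protocol does not supply and on reading p0 as a CR+PR rate. Under CR+PR only, there is no inflation and the stated design properties hold.

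The confirmation conflict is separate. Whether ORR and DoR need a confirmed response differs between sections. If confirmation were required and 90% of responses were confirmed (an assumption), power would fall from 0.803 to about 0.51, with type I error also lower.

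**What to change.** In section 10.2, delete MR from the objective-remission sentence. Define a responder there as best overall response of CR or PR by RECIL 2017, matching the synopsis and section 2, and state that this definition applies at the stage-one look and at the final analysis. Add MR to the tabulated categories as a separate non-response category beside SD.

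Decide whether response must be confirmed, and write the same rule in the synopsis, section 2, section 7.1.2, section 10.2 and section 10.4, for ORR and DoR alike. Deleting the word in section 10.4 alone would leave DoR tied to a confirmed response in three places. If confirmation is required, state how a response is confirmed and recheck power, since p0 and p1 would then need to refer to confirmed response.

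The MR correction is a wording change with no effect on sample size: type I error stays at 0.043 and power at 0.803. Dropping confirmation also costs only wording; adopting it could cost substantial power at 28 patients.

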### **Secondary outcome measures**

PFS refers to the time (in months) from the first medication to the first confirmation and recording of disease progression or death (whichever comes first). The researcher will evaluate the disease progression according to the RECIL 2017 Response Criteria for Malignant Lymphoma. During the analysis, subjects without disease progression or death will be censored on the date of the last tumor evaluation.

Subjects who have no post-baseline tumor assessment results will be censored on the first day of medication plus 1 day.

DoR refers to the time from the date of first reaching CR or PR (whichever is recorded first) to the date of first recording of disease progression or death (whichever comes first). DoR assessments were performed on subjects judged by the investigator as objective remission. During the analysis, subjects who have no disease progression or death will be censored on the last day of tumor assessment. If the tumor assessment has not been performed after the date of the first achievement of CR or PR, the date of the first occurrence of CR or PR plus 1 day is used as the censored value when calculating DoR. Kaplan-Meier method is adopted to analyze DoR and obtain survival curve.

TTR refers to the time from the first medication to the first CR or PR (whichever is recorded first). TTR will only include subjects who achieve ORR. The TTR will be summarized separately for the researcher's judgment.

OS refers to the time from the first medication to death of whatever reason. Subjects who have not been reported dead before the cut-off date will be censored on the last known survival day. If the subject has no post-baseline data, it will be censored on the day of the first medication plus 1 day. The analysis method is the same as PFS.

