| Bone marrow aspiration and biopsy  | × |   |   |   |   |   | × |   |   |  |
| Biomarker collection                            |   |   |   |   |   |   |   |   |   |  |
| Peripheral blood                   | × | × | × | × | × | × | × |   |   |  |

Note.

- End of treatment (EOT): the date of termination of study treatment is defined as the date on which the investigators confirms that the subject needs to terminate the study treatment for any reason. The time window of termination of study treatment visit is +28 days.
- Safety follow-up: the time window of safety follow-up was 30 days after the last study  $\pm$  3 days; If the study treatment termination visit occurs within the time window of safety follow-up, the same examination items need not be repeated.
- Radiography follow-up: except for the subjects who stopped taking drugs due to the judgment of disease progression according to imaging evaluation, the imaging evaluation was continued according to the established time until the occurrence of imaging disease progression, the start of new anti-tumor treatment, withdrawal of informed consent, death or the end of the study (whichever occurs first)
- Survival follow-up: after the last study, the survival of the subjects was followed up by telephone every 12 weeks, and the survival of the patients with disease progression was followed up every 8 weeks.
- Combined use of drugs: The combined medication within 30 days before the screening visit was recorded until the safety follow-up was completed.
- Adverse events: all AE were recorded from the signing of informed consent until 30 days after the last study treatment; SAE should be recorded until 90 days after the last study treatment or the start of new anti-tumor treatment, whichever occurs first. After that, only SAE related to the study treatment should be recorded.
- ECG: ECG will be in screening period, treatment period (3 weeks)  $\pm$  3 days) and safety follow-up, ECG examination can be added if necessary.
- Height, weight and vital signs: height examination was only carried out in the screening period, weight examination was only carried out in the screening period, study treatment termination visit and safety follow-up; Vital signs include body temperature, pulse rate, respiratory rate and blood pressure.

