17. Radiography evaluation: according to RECIL 2017 lymphoma criteria, the efficacy was evaluated by the researchers. During the screening period and every 6 weeks after the start of the study, enhanced PET / CT or MR or CT examinations were performed in the head and neck (including nasal cavity, hard palate, anterior cranial fossa and nasopharynx), chest, abdomen and pelvis; If you are allergic to CT contrast medium, enhanced MRI can be used. The whole body PET / CT or MR or CT examinations were performed in the screening period, 6, 12, 18 weeks after treatment, repeated every 8 weeks after 6 cycles up to 12 months. Additional PET / CT examination is required if residual lesions or suspicious progression are indicated during enhanced CT follow-up. Except for the subjects who stopped using drugs due to the progress of disease determined by imaging evaluation, imaging evaluation was continued according to the established time until the occurrence of imaging disease progression, the start of new anti-tumor treatment, withdrawal of informed consent, death or the end of the study (whichever occurs first). Within 24 months after the end of the treatment, imaging reexamination was carried out every 12 weeks, and over 24 months, reexamination was carried out every 12-24 weeks.
18. Bone marrow puncture / biopsy: bone marrow puncture / biopsy should be performed in the screening stage and when CR was judged by imaging; If it is not clear whether the bone marrow is invaded under the microscope, flow cytometry or immunohistochemistry can be performed according to the judgment of the researcher. Patients with bone marrow involvement should be reexamined every 6 weeks.
19. Biomarker detection: before each cycle of treatment.

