### **3.5 Follow-up Period**

All patients, regardless of disease status, will be visited for end of treatment within 4 weeks after the end of the study, followed every 12 weeks for up to 3 years, or until withdrawal of consent, loss to follow-up, or death, whichever occurs first. When disease assessments are not planned for a follow-up visit, the visit can be done by phone.

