## **6.4 Follow-up of progression-free survival**

Starting from 8 weeks after the last administration of the study drug, patients with stable or improving condition or those with early termination due to intolerance will be followed up for progression-free survival every 12 weeks ( $\pm 7$  days). Radiological examinations will be carried out until disease progression, death, withdrawal of ICF, start of other new treatments or end of the entire study (whichever occurs first).

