## **7.2 Evaluation of efficacy**

The efficacy of the study drug will be determined by the objective tumor evaluation made by the research center based on the RECIL 2017 Response Criteria for Malignant Lymphoma.

Radiological evaluation of tumor is determined by PET/CT, MR or CT with uniformity in evaluation method as well as machine and technical parameters throughout the study period. Unless contraindications, contrast agents should be used. The radiological results are interpreted by researchers or radiologists in each research center. If the tumor evaluation has been performed within 21 days before enrollment with the same method and machine in the same hospital, it can be used as a baseline tumor evaluation. The baseline tumor evaluation should include the nasal cavity, chest, abdomen, pelvis and any other suspected areas. If there are clinical indications, appropriate methods, such as cranial MRI, bone scan can be used to examine any other known or suspected disease sites.

From the day of the first administration, radiological examination will be performed to evaluate the tumor condition every 6 weeks (-7 days) until the completion of 6 cycles of treatment, PD, intolerable toxicity, death, investigator's decision or patient's voluntary withdrawal from the study (whichever occurs first). Repeated every 8 weeks after 6 cycles up to 12 months, or disease progression, intolerable toxicity, death, investigators' decision, or the patient's voluntary withdrawal from the study. Researchers can arrange additional radiological examinations based on the patient's clinical conditions. If the medication is suspended due to AE or other reasons, the tumor evaluation will still be carried out as originally planned. For patients who are suspected of developing PD before the next scheduled tumor evaluation, an unscheduled tumor evaluation should be performed.

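### PFS and DoR count deaths after new anti-tumor treatment as events although imaging and PFS follow-up have stopped, so unscanned time is credited only to patients who die

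*Protocol*

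**What the plan says.** **Event and censoring rule.** Section 10.2 (Secondary outcome measures) measures PFS "from the first medication to the first confirmation and recording of disease progression or death (whichever comes first". For censoring it says that "subjects without disease progression or death will be censored on the date of the last tumor evaluation". DoR has the same structure: it runs from first CR or PR to progression or death, and is censored at the last tumor assessment only if neither has occurred. New anti-tumor treatment is not mentioned for either endpoint. Read literally, one provision takes some deaths out of the PFS count: "Subjects who have no post-baseline tumor assessment results will be censored on the first day of medication plus 1 day". It concerns only patients never scanned after baseline.

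**When imaging stops.** Section 6.4 says: "Radiological examinations will be carried out until disease progression, death, withdrawal of ICF, start of other new treatments or end of the entire study". Schedule notes 3 and 17 continue imaging "until the occurrence of imaging disease progression, the start of new anti-tumor treatment, withdrawal of informed consent, death or the end of the study". Section 3.1 ends PFS follow-up itself when a patient receives another new treatment.

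**When collection of deaths stops.** Under section 3.5 all patients, whatever their disease status, are "followed every 12 weeks for up to 3 years, or until withdrawal of consent, loss to follow-up, or death". Schedule note 4 adds that "the survival of the subjects was followed up by telephone every 12 weeks". Section 6.5 gives a different limit, 2 years from first administration, for patients who have progressed and started other treatment.

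**Ways to leave without progression.** The notes to sections 5.1.1 and 5.1.2 take patients with stable disease off study. Section 6.4 foresees early termination for intolerance. Section 5.1.2 allows autologous transplant (ASCT) after 12 months in responders.

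**The concern.** Two conventions for new therapy are coherent. One follows patients for progression regardless of new therapy. The other censors at the last evaluation before it. The protocol's rules together give neither: progression is no longer looked for after new treatment, but death still counts, on its own date. Whether the unscanned interval is credited as progression-free then depends on the patient's later outcome.

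There is no control arm in which such a bias could cancel. PFS and DoR will be read against outside figures, such as the 7.0-month median PFS quoted for chidamide in section 10.1 or the statement in section 1.1 that PFS and DoR on PD-1/PD-L1 monotherapy are relatively short. An upward shift would flatter the combination.

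**Working it through.** **The plan's own figures.** The protocol plans no number of events, power or test for PFS, so there is no PFS figure to reproduce. The ORR design in section 10.1 (4/7, 19/28; 0.55 against 0.80) does reproduce: exact one-sided alpha 0.0430 and power 0.8033. No PFS quantity enters it.

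**One patient under the rules.** Assume the last scan is at week 6 (1.4 months), new therapy starts at week 8 (1.8 months), unseen progression comes 2 months later (3.8) and death 6 months after that (9.8).
- True PFS: 3.8 months.
- Section 10.2 if the patient dies within follow-up: event at 9.8 months.
- Section 10.2 if the patient is still alive at cut-off: censored at 1.4 months.

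**Inputs for the group effect.** From the protocol: median 7.0 months (section 10.1, used here for patients who stay) and scans "every 6 weeks (-7 days) until the completion of 6 cycles of treatment". Assumed, because the protocol gives no values: a share g leaves after the week-6 scan without progression and starts new therapy at week 8; median 2-4 months from then to progression; median 6-10 months from progression to death; all times exponential.

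**6-month PFS by formula**, for g = 20%, 4 and 10 months, 36 months of follow-up:
- Stayers: S0(t) = 2^(-t/7), so S0(1.38) = 0.872 and S0(6) = 0.552.
- Leavers at month 6, which is 4.16 months after new therapy: progression-free 2^(-4.16/4) = 0.486. Alive: (a·e^(-4.16b) - b·e^(-4.16a))/(a - b), with a = ln2/4 and b = ln2/10, gives 0.925. The same expression at 34.16 months gives 0.154 still alive at cut-off.
- True: 0.8 × 0.552 + 0.2 × 0.486 = 0.539.
- Censored at last scan: (0.8 × 0.872 + 0.2) × 0.552/0.872 = 0.568.
- Section 10.2 as written: 0.898 × [0.442 + 0.2 × (0.925 - 0.154)] / (0.898 - 0.2 × 0.154) = 0.617.
- The rule adds 0.617 - 0.568, about 5 points. The remaining 0.568 - 0.539, about 3 points, is informative departure, which conventional censoring does not remove.

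**Full range by simulation** (400,000 patients per scenario, Kaplan-Meier, 36 months):

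| g | Median PFS, months: true / censored at last scan / as written | Rule adds to median | 6-month PFS, %: true / censored / as written | Rule adds, points |
|---|---|---|---|---|
| 5% | 6.7-6.9 / 7.1 / 7.3 | 0.2-0.3 | 54-55 / 56 / 57 | about 1 |
| 10% | 6.4-6.8 / 7.1 / 7.4-7.7 | 0.3-0.6 | 52-55 / 56 / 58 | 1.7-2.4 |
| 20% | 5.8-6.7 / 7.3 / 7.9-8.5 | 0.6-1.2 | 49-54 / 57 / 60-62 | 3.3-4.8 |

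With 24 months of follow-up the rule adds 0.2-0.4 months and 1.4-1.9 points at g = 10%, and 0.5-0.8 months and 2.8-3.8 points at g = 20%. For scale, the standard error of 6-month PFS at n = 28 is √(0.57 × 0.43/28), about 9 points.

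**A milder model.** If leaving is unrelated to progression (10-40% leave, median 3-12 months from progression to death, 24-month cut-off), affected patients who die are recorded as events on average 2.8-5.8 months late. They are about 4-30% of the arm. PFS at 12 months is 0.34-0.37 as written, 0.33-0.34 had imaging continued, and 0.32-0.33 censored at the last scan. The direction is the same; the net excess over continued imaging is about 0.5-4 points.

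**The case against.** **Sections 3.1 and 6.4 already close PFS observation at new treatment**, so a patient without progression by then could be read as censored at the last evaluation. That is a sensible intention and it favors the fix below. But section 10.2 is the analysis rule. It counts death without limit, and the only patients it censors at the last evaluation are those with neither progression nor death. An analyst who follows it literally gets the biased result.

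**Such detail may be left to the SAP.** Silence could be. Here the protocol fixes an event definition and a censoring rule that do not fit its own imaging schedule.

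**The effect is easily overstated.** This stands. A reader might infer that the whole gap between true PFS and PFS as written (7-12 points at 6 months for g = 20%) is due to the rule. In the working, between about 40% and 70% of that gap is informative departure and remains under conventional censoring. A reader might also take the 20% of non-responders implied by the 80% target ORR as the share affected. Non-responders include patients with progression, who already have an event, and nothing in the protocol says that all the others start new treatment early. Nor do all leavers get longer times: only those who later die within follow-up do.

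**PFS and DoR are secondary and descriptive.** This also stands: no test or decision depends on them.

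**Conclusion.** The concern holds in a limited form. The protocol stops looking for progression at new anti-tumor treatment but keeps counting later deaths as PFS and DoR events, which biases both upward. If 10-20% of patients leave without progression and start other therapy, the rule adds about 0.3-1.2 months to median PFS and about 2-5 points to 6-month PFS relative to censoring at the last scan, at 36 months of follow-up. This is about half a standard error or less at n = 28. It is smaller with fewer leavers or shorter follow-up. The leaving share and the times to progression and death are assumptions; the direction does not depend on the particular values tried. DoR shares the wording and so the defect, but its size was not calculated.

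ORR, its decision rule and the sample size are untouched. The point deserves correction because the remedy is cheap, not because the trial's main conclusion is at risk.

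**What to change.** In section 10.2, state that subjects who start new anti-tumor treatment before documented progression are censored for PFS and DoR at the last tumor evaluation before that treatment, even if they die later. State also whether ASCT after 12 months counts as new treatment for this purpose. Report the number of subjects so censored. Give the rule as now written, with all deaths counted, as a sensitivity analysis.

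This matches the point at which sections 3.1 and 6.4 already stop PFS follow-up. Counting progression regardless of new therapy, with dates taken at the survival contacts, is less suitable: section 10.2 requires progression to be judged by RECIL 2017, and those contacts are by telephone.

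The cost is a few sentences. No scans or visits are added, and the schedule already records new antineoplastic therapy during follow-up. The downsides are fewer PFS and DoR events and some remaining informative censoring, which is why the count and the sensitivity analysis should be shown.
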